##### Maintenance

Maintenance can be defined as the extent to which a program is sustained over time, at both the individual and the organization level [70]. As the evaluation process will take place immediately post-intervention, it will not be possible to measure maintenance over time. However, the intention to maintain the program beyond initial implementation, will be assessed at the teacher and student levels. Teachers will be asked: “*will you continue implementing the FEAST program in your classroom?*” and depending on their response (‘Yes/No’), the appropriate open-ended question will also be asked: “*what motivates/inspires you to continue implementing the FEAST program in your classroom?*” or “*what are the reasons you would not continue to implement the FEAST program in your classroom?*” For the students, they will be asked: “*would you like to do the FEAST program again?”*

##### Program satisfaction (teacher and student)

To assess satisfaction, the teachers will be asked: if they felt the training was effective and whether it helped prepare them to deliver the program within the classroom setting; to rate the effectiveness of the resources provided; whether the program met Grade 5–6 KLAs, aligned with the cross-curricular priority of sustainability and general capabilities and whether it was easy to implement STEM lessons; whether it met their student’s learning needs; and whether it was easy to integrate the program into the classroom routine. Teachers will also be asked whether they thought their students found the activities and website easy to follow and resources engaging.

To assess satisfaction, students will be asked whether: FEAST activities and website were easy to read and understand; if they thought the program was fun; if they enjoyed cooking; if they cooked some of the classroom recipes at home; whether they learnt anything new about food preparation and cooking; and whether they created a cookbook and if so, if they enjoyed creating it. Both student and teacher post-FEAST surveys ask them to rate how likely they would recommend the FEAST program to others.

##### Program perceived benefits (teacher and student)

The teachers will be asked whether they thought their students understood the importance of being aware of food waste; the impact of food waste locally and globally; and whether students understood which behaviours could reduce food waste in the home and at school. Teachers will also be asked whether they thought: students understood where food comes from; were making healthy food choices; understood how to prepare and cook food; were eating more F&V and less junk food; and were reducing food waste behaviours (and by how much i.e. what percentage reduction). There is also one open-ended question asking students to name one new thing they learnt during the cooking activities.

### Participant timeline

For the intervention school groups, all baseline (i.e. pre-intervention) student surveys will be issued in week one of the school term in which the FEAST program will be implemented (i.e. Timepoint 1: T1). Post-intervention student surveys will be issued in the last week of the same school term (i.e. Timepoint 2: T2). Figure 3 outlines the trial timeline for school enrolments, intervention delivery and data collection throughout 2021.

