### Trial design

This study will employ a pragmatic approach, involving a parallel, cluster, non-randomized controlled trial (NRCT) with pre- and post-measures. It will involve 20 primary schools (10 intervention vs 10 wait-list control) with children in Grades 5–6, aged 10–12 years, within NSW, Australia. Schools that have self-selected to undertake the FEAST program in 2021 will be invited to participate in this trial.

OzHarvest, a not-for-profit community-based, food-rescue organization, has designed the FEAST program and has been training teachers to implement the program within the classroom setting, in Australian primary-schools, since 2018. The intervention runs for one school term, approximately 10 weeks. Schools participating in the FEAST program during Term 2 (19 April-25 June) of the 2021 scholastic school year will be invited to act as the intervention schools for this trial. Pre- and post-intervention surveys will be issued in the first and last weeks of term, respectively.

Schools participating in the FEAST program during Term 3 (12 July-17 September) and Term 4 (5 October-17 December), will be invited to act as the comparator group (i.e. wait-list control schools). The wait-list control schools will continue with their usual academic programs and will complete the surveys at the same time as the intervention schools (i.e. during the first and last weeks of Term 2). When the wait-list control schools undertake the FEAST program during their chosen school term (Terms 3 or 4), they will be issued with the post-intervention surveys again (third data collection point [T3]), only if they are willing to complete the surveys for their own interest. Previous experience suggests obtaining a third wave of follow-up data from schools is challenging and hence this will not be compulsory. Given variations in the timing of administration and likely low response rates, these data will be used for school feedback only, and not included in the trial.

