OzHarvest provides training, resources and support to teachers to deliver a recommended 1.5-h lesson/week, for a 10-week unit of inquiry (incorporating 10 theory and six practical activities) within the classroom setting. The FEAST program has been integrated with lessons mapped to the Australian Curriculum, embracing Grade 5–6 key learning areas (KLAs) i.e. English [44]; STEM (Science, Technology, Engineering, and Mathematics) curriculum [45]; general capabilities (Literacy, Numeracy, Information and Communication Technologies, Critical and Creative Thinking, Personal and Social Capability and Intercultural Understanding) [46]; and the cross-curriculum priority of sustainability [47]. FEAST has been aligned with the Australian Dietary Guidelines and state/territory-based healthy eating strategies [1], with all recipes including either fruits and/or vegetables (which are also the two most wasted food groups [48]). The program includes a range of educational resources designed to assist in the delivery of the theory and practical components as outlined in Additional file 2 [49]. The lesson plan topics are outlined in Additional file 3 and the practical guide components are outlined in Additional file 4.

Grade 5–6 classroom teachers from the schools that volunteer to participate in the FEAST program, will be invited for a training workshop at OzHarvest offices. A Professional Learning Program will be delivered over six hours of face-to-face training. During the training day, two FEAST education team members will train the teachers in food preparation and cooking skills (making the hot and cold recipes designed for the FEAST program). To assist the teachers and students during the class practical components, teachers will be provided with instructions and resources to seek volunteers throughout the school community such as parents/caregivers, grandparents, and/or school staff etc. Trained volunteers will also be available through OzHarvest, to assist during the practical components. It is recommended that the teachers organize at least one adult per five students, for each of the practical sessions, in addition to themselves.

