##### Nutrition (F&V consumption, variety and knowledge)

The proportion of children consuming the recommended two serves of fruit/day will be calculated. According to the Australian Bureau of Statistics, only 6.3% of children meet their recommended intake of five vegetables/day, with an average intake of only two serves/day [7]. Therefore, a more conservative level of two serves/day will be used to assess changes in proportion of students consuming vegetables. For analyses involving proportions, intakes of F&V will be dichotomized to 0–1 serves/day verses ≥2 serves/day. These outcomes will be calculated using the same two questions used for the primary outcomes.

Vegetable variety (number of different types of vegetables consumed yesterday), fruit variety (number of different types of fruits consumed yesterday), and the mean number of the variety of the different F&V consumed, will be calculated (with 95% CI), as well as the proportion (in percentages %) of students consuming these F&V. To capture variety of F&V eaten by children, two questions were taken from the *Modified Child Nutrition Questionnaire* (MCNQ) [56], which was designed to assess dietary patterns in Australian children aged 9–13 years, and has face/content validity, criterion/concurrent/predictive validity and reliability [55]. However, there has been an addition of ‘other’ under the list of fruits and vegetables listed in these questions, with the opportunity to state which ‘other’ F&V children consume. This was used in order to capture the different varieties of F&V consumed by children from culturally and linguistically diverse (CALD) backgrounds. The inclusion of questions that are sensitive to populations that are CALD, was one of the lessons learnt from the FEAST pilot study, given the schools that participated in the pilot, had a high percentage of students that were from diverse ethnic backgrounds, as well as a small percentage of students from Indigenous backgrounds.

Nutrition knowledge will be calculated as the proportion (%) of students reporting knowing the recommended intakes of fruit and vegetable serves/day. Questions for this outcome were also taken from the MCNQ [56], however the multiple-choice responses were modified and simplified to include only specific servings/day with the exclusion of responses that included servings/week.

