##### Food production (knowledge)

Understanding of the ‘farm to plate’ concept, will be calculated as the proportion (%) of students reporting the correct sequence of a strawberry’s journey from farm to plate. The question for this outcome was also specifically developed for the FEAST program and was aligned with the food production lesson.

A combination of dichotomous (yes/no) responses, multiple choice options, Likert scale questions and short sentence answers, make up the surveys. Each survey question has been written in simple language and several questions are accompanied with an illustration to enhance understanding, such as F&V serving sizes. In addition, two posters with the images of the F&V that appear in the questions relating to F&V variety, will be provided to the teachers to display them in the classroom, so that students have additional visual aids to assist them with the F&V questions. For ease of use, the survey was created within the electronic data capture system called REDCap, which will entail the self-reported pre- and post-intervention surveys, which should take between 20 and 30 min to complete. Children aged 10–12 years of age, are capable of self-reporting constructs like these [65].

In order to enhance successful completion of the FEAST survey, the following evidence-based recommendations have been included: short completion time [66]; training of teachers to explain questions and monitor children [65]; use of visual prompts [65, 67]; use of technology, such as online surveys [68]; and reduced retention interval, by asking children to recall what they ate in the previous 24 h [69].

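### The post survey follows directly on the end of the program, so the variety outcomes, which ask about yesterday, can count food made in a FEAST class held the day before

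*Protocol article*

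**What the plan says.** All references are to the Protocol article, Methods.

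- **Survey timing.** Trial design: "Pre- and post-intervention surveys will be issued in the first and last weeks of term, respectively". Participant timeline: "Post-intervention student surveys will be issued in the last week of the same school term". Data collection methods adds that T2 is done once the program is complete, at a time the teacher arranges for the class.
- **Program length.** Trial design: "The intervention runs for one school term, approximately 10 weeks". Intervention schools deliver it in "Term 2 (19 April-25 June) of the 2021 scholastic school year". Intervention recommends a "1.5-h lesson/week, for a 10-week unit of inquiry (incorporating 10 theory and six practical activities").
- **Food in class.** Intervention describes the program "with all recipes including either fruits and/or vegetables".
- **Recall window.** Secondary outcomes, Nutrition: "Vegetable variety (number of different types of vegetables consumed yesterday), fruit variety (number of different types of fruits consumed yesterday"). A general list of survey-design measures at the end of the Food production section includes "reduced retention interval, by asking children to recall what they ate in the previous 24 h". Primary outcomes takes the two serves/day items from a food frequency questionnaire and gives no recall window for them.
- **Controls.** Wait-list schools are surveyed in the same weeks and follow their usual teaching (Trial design).

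**The concern.** The program and the term are equally long, and T2 comes in the final week. A class that keeps to the weekly schedule therefore finishes the program and answers the survey within a few days. A one-day recall window is then sensitive to what happened in the last session. If that session was a practical on the day before the survey, the child may correctly report food that the lesson supplied.

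This matters because the stated aim is to learn whether the program raises children's consumption, with fruit and vegetable variety as a named secondary objective. Food prepared in a lesson is no longer supplied once the unit ends. Control children have no such lesson, so any contribution arises in one arm. Allocation is by self-selection and participants are not blinded, so a one-sided measurement artefact that can be foreseen is worth closing before data are collected.

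**Working it through.** **1. Calendar.** From 19 April to 25 June 2021 there are 12 + 31 + 25 = 68 calendar days, Monday to Friday. 68 = 9 × 7 + 5, which is 10 school weeks and agrees with the plan's own figure of about 10 weeks. T1 is in week one, before the program starts. Ten weekly lessons in 10 weeks leave 10 − 10 = 0 spare weeks, so a full schedule ends in the week of T2. A class that compresses or drops lessons may finish earlier.

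**2. Is the last session a practical?** The article gives 10 theory and six practical activities but does not place them in weeks. The lesson topics and practical guide are in Additional files 3 and 4, which are not shown. A final-week practical is possible and is not established.

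**3. Recall window, outcome by outcome.**

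| Outcome | Window stated | Exposed when |
|---|---|---|
| Fruit variety, vegetable variety | Yesterday | A practical was held on the preceding calendar day |
| Fruit and vegetable serves/day (primary), and the proportions built from the same two items | None stated for the items | If 24-hour recall: a practical fell in the 24 hours before the survey. If usual intake: diluted over the period asked about |

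For the usual-intake case, six practicals fall on at most 6 of 68 days (6/68 = 8.8%), so class food would move a daily average little.

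**4. Which arm, which time.**

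| | T1 | T2 |
|---|---|---|
| Intervention | No FEAST cooking yet | Class food possible |
| Control | None | None |

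The planned model compares arms at T2 adjusted for the baseline value. The baseline value contains no class food in either arm, so conditioning on it leaves any T2 contribution in the intervention estimate.

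**5. Size.** Write the contribution as b = p × a × (1 − d), where p is the share of intervention children whose recall day contains a practical, a is the amount (types or serves) eaten in class, and d is the part they would have eaten anyway or that replaced other food. The article gives none of the three, nor does it say outright that children eat what they cook. With p = 0 there is no effect. With p above 0 and d below 1, b is positive and favours the program. Because a recipe may contain fruit, vegetables or both, b can differ between the fruit and the vegetable outcomes. No figure for b is supportable.

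**6. Could it be detected afterwards?** The teacher items described under Implementation ask how many cooking sessions were held. No date is mentioned, so affected classes could not be identified from the data described.

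**The case against.** Several stronger readings are tempting, and the article does not support them.

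- *That the program is still running at T2.* Data collection methods places T2 at program completion. What remains is a final practical shortly before the survey.
- *That the primary outcomes are inflated.* The 24-hour phrase stands in a general list and names no question; the variety items alone could account for it. The primary items come from a food frequency questionnaire, and their wording is in Additional file 5, which is not shown. The primary outcomes are exposed to the same degree only under 24-hour recall.
- *That a number of serves or types can be attached.* It cannot, for the reasons in step 5 of the working.
- *That the sections contradict one another.* They do not; the overlap comes from combining them.

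It can also be said that the objective is immediate effectiveness in a pragmatic trial, and that the Discussion counts exposure to fruit and vegetables among the program's components, so food eaten in class is part of the effect. That is a defensible choice of estimand. It has not been stated, however, and whether class food enters would depend on the day each teacher happens to choose.

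Finally, instructions on the survey day are operational detail that an article may leave out. That is fair and lowers the weight of the point. The article does, however, fix the survey week, the program length, the variety recall window and the teacher's choice of slot, and together these allow the overlap.

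**Conclusion.** The point holds as a possibility built into the design. A class surveyed the day after its last practical follows the plan as written, yet its variety answers can include food made in the lesson. This can happen only in the intervention arm and only at T2, and baseline adjustment does not remove it.

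The exposure is firm for the two variety outcomes. For the serves/day outcomes it is conditional on 24-hour recall, and small if the items ask about usual intake. The direction favours the program, assuming that children eat at least some of what they cook and that it does not merely replace other fruit and vegetables. The size is unknown. This is an inexpensive improvement to data collection; it does not show that the results will be biased.

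**What to change.** 1. Keep T2 in the last week. Instruct teachers to hold it on a day when no FEAST practical took place earlier that day or on the preceding calendar day. With Friday as the latest survey day, the last practical would fall no later than Wednesday of that week. No other limit on the weekday is needed; for a Monday survey, yesterday is a Sunday and cannot include class cooking.
2. Add the date of the last practical to the existing teacher post survey, to be set against the date on which the class completed T2.
3. Repeat the variety analyses without classes surveyed within one day of a practical, and do the same for intake if the primary items use 24-hour recall. Label this supportive only: it excludes classes on a post-baseline event that can occur in one arm alone, so it does not replace the intention-to-treat result.

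The cost is one line of instructions, one survey item and one extra analysis, with no change to sample size, instrument or survey week. The downside is slightly less freedom for teachers in choosing the survey day. A class that cannot comply is still surveyed and is identified by the recorded date.

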**Fig. 3 Fig3:**
[figure not shown]
Timeline of school enrolments, intervention delivery and data collection. Legend: PI Primary Investigator (FK); Int Intervention group; WLC Wait-list control group; T1 Timepoint 1; T2 Timepoint 2; T3 Timepoint 3

### Sample size

Sample size requirements estimated that 20 schools (10 per intervention arm) will be required to take part in this study, with an average of 50 students (SD ± 22, and therefore CV = 0.436) per arm. These numbers are feasible given that more than 30 schools have enrolled to participate in the program with OzHarvest, for 2021, and recruitment continues. A within-school intraclass correlation of 0.04 is estimated for both primary outcomes of fruit and vegetable intakes [71–73] and correlations of 0.5 are assumed between outcome measures between baseline and 10 weeks [56]. Standard deviations for vegetable and fruit serves/day are estimated to be 1.3 and 1.1 respectively, according to the South Australian Health Reports from 2015 on children’s vegetable intake [74] and fruit intake [75]. Allowance will be made for 20% loss due to follow-up or missing data [72, 76].

Given there are two primary outcomes (fruit serves/day and vegetable serves/day), a Bonferroni-corrected alpha (α) of 0.025 (i.e. 0.05/2) will be used. An increase of 0.5 servings of fruit/day (i.e. 75 g) and vegetables/day (i.e. 37.5 g) may be considered meaningful [56, 77], given that even small increases (e.g. 50 g/day) in combined F&V intakes have the potential to provide protection against the development of certain NCDs [77]. Under the above assumptions, the study would provide 90% power to detect an intervention effect of this size, for the vegetable intake primary outcome and 97% power for the fruit intake primary outcome.

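### Sample size: the average of 50 students is labelled per arm, but the stated 90% and 97% power is obtained only with about 50 per school (a unit error)

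*Protocol article*

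**What the plan says.** All the figures are in the Sample size section of the protocol article. On clusters it states that "20 schools (10 per intervention arm) will be required to take part in this study". The number of students follows in the same sentence and is given as an average for each arm: "with an average of 50 students (SD ± 22, and therefore CV = 0.436) per arm". The other inputs are:

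- clustering: "A within-school intraclass correlation of 0.04 is estimated for both primary outcomes"
- repeated measures: "correlations of 0.5 are assumed between outcome measures between baseline and 10 weeks"
- spread: "Standard deviations for vegetable and fruit serves/day are estimated to be 1.3 and 1.1 respectively"
- loss: "Allowance will be made for 20% loss due to follow-up or missing data"
- a Bonferroni-corrected alpha of 0.025 for each of the two primary outcomes, and a target difference of 0.5 serves/day for each.

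From these the section concludes that "the study would provide 90% power to detect an intervention effect of this size, for the vegetable intake primary outcome", with 97% for fruit. The Statistical analysis section confirms that models adjust for the baseline value of the outcome and include a random intercept for school. The Abstract and Trial design sections give the number of schools but no number of students, so this sentence holds the article's only student sample size.

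**The concern.** With 10 schools in an arm, 50 students per arm means 5 per school. That is ten times fewer than 50 per school, and the quoted power does not belong to it. The descriptors attached to the 50 point the same way. A mean with an SD and a CV describes how cluster sizes vary, and the CV enters a cluster power calculation only as variation in school size. Two arms have no useful average size with a CV.

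The sentence matters because nothing else in the article corrects it. The remark on feasibility follows directly from it, and the Discussion relies on the trial being well powered. Anyone who checks recruitment, or later compares the report with the protocol, would work from a target of 100 children instead of roughly 1,000.

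**Working it through.** **Inputs** (Sample size section unless noted): k = 10 schools per arm; ICC 0.04; CV 0.436; baseline to follow-up correlation 0.5; SD 1.3 (vegetables) and 1.1 (fruit); difference 0.5; alpha 0.025; loss 20%. Baseline adjustment is from Statistical analysis. Assumed, because not stated: a two-sided test, and the power formula.

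**Formulas**, with m students per school:

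- Design effect allowing for unequal school sizes: DE = 1 + [(1 + CV²)m − 1] × ICC.
- Alternative, the relative-efficiency correction: DE = [1 + (m − 1) × ICC] / [1 − CV² × L(1 − L)], with L = m / [m + (1 − ICC)/ICC] = m/(m + 24).
- Variance of the difference = 2 × SD² × (1 − 0.5²) × DE / (k × m).
- Power from the noncentral t with 2 × 10 − 2 = 18 df (critical value 2.445), or from the normal (2.241).

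**The plan's own figure first: 50 per school**

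- No loss, m = 50: DE = 1 + (1.190 × 50 − 1) × 0.04 = 3.34. Vegetables: variance = 2 × 1.69 × 0.75 × 3.34/500 = 0.0169, SE 0.130, and 0.5/SE = 3.84. Fruit: 2 × 1.21 × 0.75 × 3.34/500 = 0.0121, SE 0.110, ratio 4.54. Power **90.7% / 97.6%**.
- After loss, m = 40: DE = 2.86 and ratios 3.71 and 4.39. Power **88.6% / 96.6%**.
- After loss with the relative-efficiency correction: DE = 2.68 and ratios 3.84 and 4.54. Power **90.7% / 97.5%**.

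**As printed: 50 per arm**

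- No loss, m = 5: DE = 1 + (1.190 × 5 − 1) × 0.04 = 1.20. Vegetables: variance = 2 × 1.69 × 0.75 × 1.198/50 = 0.0607, SE 0.246, ratio 2.03. Fruit: SE 0.209, ratio 2.40.
- After loss, m = 4: DE = 1.15 and ratios 1.85 and 2.19.

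| Reading of the 50 | Loss | Calculation | Vegetables | Fruit |
|---|---|---|---|---|
| Per arm | none | t, 18 df | 36% | 50% |
| Per arm | 20% | t, 18 df | 30% | 42% |
| Per arm | none | normal | 42% | 56% |
| Per arm | 20% | normal | 35% | 48% |
| Per school | none | t, 18 df | 90.7% | 97.6% |
| Per school | 20% | t, 18 df | 88.6% | 96.6% |
| Per school | none | t, relative efficiency | 92.9% | 98.4% |
| Per school | 20% | t, relative efficiency | 90.7% | 97.5% |
| **Stated** | – | – | **90%** | **97%** |

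**Can another convention rescue 50 per arm?** Ignoring clustering altogether, with all 50 analysed, gives 49% / 65%. A one-sided 0.025 test (normal, after loss) gives 46% / 59%. Neither comes near 90% / 97%.

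**Check on the CV.** 22/50 = 0.44, which agrees with "SD ± 22, and therefore CV = 0.436" up to rounding. The CV was thus formed around the 50, so the 50 is the mean of whatever varies with SD 22. In this calculation that is school size.

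**The case against.** The best defence is that any informed reader can recover the intended unit from the sentence itself. The SD and CV signal cluster size, and feasibility is argued from the number of schools enrolled. Other sections describe whole Grade 5–6 classes receiving the survey link, with parents able to opt out. Five children per school is not a plausible working target, so the chance of recruitment actually stopping at 100 is small. This stands, and it is why the point concerns a wrong unit and not the design. It does not remove the error: the figure is stated, it is wrong, and no other figure in the article replaces it.

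A reader might draw two stronger conclusions, and the article supports neither.

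- *That the trial has only 30–50% power.* This would hold only if 50 per arm were the real target. The stated power and the CV both indicate that the calculation used 50 per school.
- *That the 90% must be lowered to 89% to allow for loss.* The 88.6% depends on one choice of design-effect formula. With the relative-efficiency correction, the same inputs after 20% loss give 90.7% / 97.5%. The article names no formula, so it does not exclude this one. It also lists the loss allowance among the assumptions before it gives the power, so the natural reading is that loss is already included.

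What remains open is narrower: whether 50 is the enrolled or the analysed average.

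**Conclusion.** The words per arm are wrong, and the stated power depends on a different unit. As printed, the inputs give about 30–42% power for vegetables and 42–56% for fruit. With 50 per school they give about 89–91% and 97–98% (t on 18 df, before or after loss depending on the formula), and up to 93% and 98% before loss with the relative-efficiency correction. The published 90% and 97% are consistent with 50 per school. This is a unit error in the only student number given, not an underpowered design.

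The result assumes a two-sided test and a baseline-adjusted analysis. The second is what the Statistical analysis section specifies. A change-score analysis has a variance factor of 2 × (1 − 0.5) = 1 in place of 0.75. With t and the first design effect it would give 77–80% / 90–92% at 50 per school and 23–27% / 32–38% at 50 per arm. The contrast between the two readings therefore does not depend on that choice.

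**What to change.** In the Sample size section, replace per arm with per school, say whether 50 is the enrolled or the analysed average, and give the totals that follow:

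- if enrolled: 50 × 10 = about 500 per arm and 1,000 overall, with 500 × 0.8 = about 400 per arm analysed after 20% loss;
- if analysed: 50/0.8 = 62.5 per school, so about 1,250 enrolled overall.

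The authors must confirm which applies, since the article does not settle it. The 90% and 97% need not be restated unless the authors' own formula gives a different value. The change costs one corrected sentence. The number of schools, the alpha, the target difference and the analysis model are unaffected.
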